## Abstract

**Background:** Intravenous tranexamic acid (TXA) within 3 hours of birth significantly reduces death due to bleeding in women with postpartum haemorrhage (PPH). Most PPH deaths occur in the first hours after giving birth and treatment delay decreases survival.  One barrier to rapid TXA treatment is the need for intravenous injection. Intramuscular injection and oral solution of TXA would be easier and faster to administer and would require less training. However, the pharmacokinetics (PK), pharmacodynamics and safety of TXA administered by different routes in pregnant women have not been established. The main aim of this study is to ascertain whether IM and oral solution of TXA will be absorbed at levels sufficient to inhibit fibrinolysis in pregnant women.

**Methods:** WOMAN-PharmacoTXA is a prospective, randomised, open label trial to be conducted in Zambia and Pakistan.  Adult women undergoing caesarean section with at least one risk factor for PPH will be included.  Women will be randomised to receive one of the following about 1 hour prior to caesarean section: 1-gram TXA IV, 1-gram TXA IM, 4-grams TXA oral solution or no TXA. Randomisation will continue until 120 participants with at least six post randomisation PK samples are included. TXA concentration in maternal blood samples will be measured at baseline and at different time points during 24 hours after receipt of intervention. Blood TXA concentration will be measured from the umbilical cord and neonate.

The primary endpoint is maternal blood TXA concentrations over time. Secondary outcomes include umbilical cord and neonate TXA concentration D-dimer concentration, blood loss and clinical diagnosis of PPH, injection site reactions and maternal and neonate adverse events.

**Discussion:** The WOMAN-PharmacoTXA trial will provide important data on pharmacokinetics, pharmacodynamics and safety of TXA after IV, intramuscular and oral administration in women giving birth by caesarean section.

**Trial registration:** ClincalTrials.gov,
NCT04274335 (18/02/2020).

## Abbreviations

BIC: Bayesian Information Criterion; CHMP: Committee for Medicinal Products for Human Use; CI: Chief Investigator; CI: Confidence Interval; Cmax: Maximum Concentration; COV: Covariate; CS: Caesarean Section; CRF: Case Report Form; CTU: Clinical Trials Unit; DMC: Data Monitoring Committee; EMA: European Medical Agency; FBC: Full Blood Count; g: Gram; GCP: Good Clinical Practice; h: Hour; ICH-GCP: International Conference on Harmonisation-Good Clinical Practice; IM: Intramuscular; IMP: Investigational Medicinal Product; IV: Intravenous; L: Litre; LMICS: Low and Middle-Income Countries; LSHTM: London School of Hygiene & Tropical Medicine; MCMC: Markov Chain Monte Carlo; MedDRA: Medical Dictionary for Regulatory Activities; min: Minute; mg: Milligram; mL: Millilitre; µL: Microlitre; OR: Odds Ratio; PD: Pharmacodynamics; PI: Principal Investigator; PK: Pharmacokinetics; PPH: Post-Partum Haemorrhage; PWR: Power; RCT: Randomised Control Trial; RR: Relative Risk; SAEM: Stochastic Approximation Expectation Maximization; SUSAR: Suspected Unexpected Serious Adverse Reaction; TXA: Tranexamic Acid.

## Background

Postpartum haemorrhage (PPH) is a leading cause of maternal mortality and morbidity. About 14 million women suffer a PPH every year after childbirth and about 100,000 die if bleeding is not controlled
^
1
^. Most PPH deaths occur in low- and middle-income countries (LMICs)
^
2–
5
^. Of those who survive, many suffer severe morbidity and need major interventions to control bleeding, including exploratory laparotomy, brace sutures and hysterectomy.

Tranexamic acid (TXA) is an antifibrinolytic drug. It binds to the lysine receptors on plasminogen blocking the conversion from plasminogen to the proteolytic enzyme plasmin, thereby preventing fibrin degradation and stabilising blood clots
^
6,
7
^. Intravenous TXA reduces blood loss in surgery and increases survival in traumatic bleeding and PPH. The WOMAN trial showed that giving intravenous TXA reduced the risk of death from PPH
^
8
^. TXA treatment, as early as possible and no later than 3 hours, reduced PPH deaths by one third and the need for laparotomy to control bleeding by over one third.

Most deaths from PPH occur within the first hours after giving birth. The survival benefit of TXA reduces by 10% with every 15 minutes of treatment delay, and after 3 hours there is no benefit
^
9
^. The need for intravenous administration of TXA is one of the main barriers for rapid treatment. Currently, TXA for PPH can only be given where trained healthcare professionals are available to give the drug intravenously. However, in many LMIC countries, a large number of women give birth at home with no access to trained personnel. Additionally, many nurses and midwives who care for women with PPH are not trained to give intravenous drugs.

 Alternatives routes to IV TXA would make administration easier and faster and would require less training. TXA is available for oral administration (tablet and solution) and has the potential to be given by intramuscular injection.

However, there has been little research into different routes of administration and the pharmacokinetic (PK) properties of TXA in pregnant women have not yet been established.

Studies in healthy volunteers show that therapeutic plasma TXA levels (plasma TXA >10 mg/L)
^
10
^ are reached rapidly (within 30 min) after IM injection
^
11–
13
^. PK modelling of the oral administration of 4 g of TXA resulted in a plasma concentration of 10 mg/L within 15 min (data on file). If absorption was similarly rapid in pregnant women, this would strongly suggest the IM and oral routes as potential alternatives to IV use.

Recently, the Trauma-INTACT trial (ClinicalTrials.gov:
NCT03875937) assessed the PK of TXA administered intramuscularly in bleeding trauma patients
^
14
^. The study found that the time to reach therapeutic concentrations of 10 mg/L after intramuscular injection of 1 g TXA was within 15 min. Additionally, it was well tolerated with only mild injection site reactions and no serious adverse events reported. The PharmacoTXA trial (ClinicalTrials.gov:
NCT03777488) has assessed the PK of TXA administered intramuscularly or orally in healthy volunteers. An ongoing RCT called TRACES (TRAnexamic Acid to Reduce Blood Loss in Hemorrhagic CESarean Delivery) aims to assess the PK and pharmacodynamics (PD) effects of two doses of TXA (0.5 and 1 g) injected intravenously in women with an ongoing PPH after delivery
^
15
^.

Physiologic changes induced by pregnancy and childbirth
^
16
^ may alter the PK and PD properties of medicines, in particular due to the increase in renal elimination clearance and volume of distribution.

PPH can occur without warning in most women. However, some risk factors such as multiple pregnancy, macrosomia or previous PPH, are known to be associated with an increased risk of PPH
^
17,
18
^.

In this study we will assess the PK, PD, safety and efficacy of TXA administered by IV, IM or oral routes in women giving birth by caesarean section (CS) with at least one risk factor for PPH. Blood samples will be taken from the women immediately before the administration of TXA (1 hour before CS) and at different time points during 24 hours after receipt of intervention. Blood samples from the umbilical cord after clamping and from newborns (obtained from the sample taken for routine heel prick test) will be taken to measure the amount of TXA transferred from the mother to the neonate via the placenta. The efficacy of the different routes of TXA administration in preventing blood loss, reducing fibrinolytic activity, and the safety of the interventions will be evaluated.

## Rationale

### Hypothesis

We hypothesise that IM and oral solution of TXA will be well absorbed in pregnant women. Based on PK modelling of data available in the literature, we predict that a 1 g IM injection or 4 g oral solution administration of TXA will provide therapeutic TXA levels ≥10 mg/L in plasma
^
10
^ within about 30 minutes. 

### Description of trial population

Recruitment will continue until 120 adult women who are undergoing CS with at least one risk factor for PPH and who complete the trial are included. 30 women will receive 1 gram of TXA by IV injection, 30 women will receive 1 gram of TXA by IM injection, 30 women will receive 4 grams of TXA orally, and 30 women will receive no TXA about 1 hour prior to the CS. Additionally, women will receive routine interventions for active management of 3
^rd^ stage of labour and if they develop PPH, all standard interventions should be given. There are no restrictions on treatment of co-morbidities.

### Description of investigational product and justification of the dosage, route of administration, administration schedule and treatment duration

In this study, women will be randomised to four groups:

1.
**IV TXA GROUP:** 30 women will receive 1 g of TXA by IV route. IV TXA treatment rapidly achieves the plasma levels of TXA needed to inhibit fibrinolysis and prevent excessive bleeding. Pharmacological research has shown that an IV dose of 1 g TXA maintains therapeutic plasma levels for around 3 hours, the period when the risk of bleeding is greatest
^
12,
19
^. However, the TXA PK and PD in pregnant women has not been described so far.2.
**IM TXA GROUP:** 30 women will receive 1 g of TXA by IM route. Studies of IM TXA in healthy volunteers report good absorption and no adverse effects
^
11,
12
^. The dose will be given as two 5 mL (0.5 g each) injections into the thigh (rectus femoris or vastus lateralis) or buttocks (gluteal muscles) muscles, depending on a clinical assessment of muscle mass
^
12
^. The 1 g dose (10 mL) is divided to reduce the volume injected (5 mL is considered the upper limit)
^
20
^. The injections will be given using the most appropriate needle size for IM administration from the sites stock (1" between 19 - 25 gauge and from 1 ½ inches up to 3" for large adults) using the Z-track method to seal the medication in the muscle
^
20
^.3.
**TXA SOLUTION ORALLY:** 30 women will receive 4 g of TXA oral solution. The dose was selected because of the 50% oral bioavailability and because previous and preliminary PK data show that the absorption through the oral route is much slower than through the IV or IM routes, with much lower maximal concentration (Cmax)
^
12,
13,
19,
21
^. Therefore, higher doses are needed to reach therapeutic levels, according to simulations. The oral route (tablets or solutions) is well characterised
^
22–
24
^, but oral TXA PK and PD in pregnant women have not been described so far.4.
**NO TXA CONTROL:** 30 women will receive no TXA and will be the control group for PD, blood loss and safety data.

### Safety of TXA and potential benefits and risks for study participants

TXA has been in clinical use for decades and has a good safety profile. TXA reduces the risk of death due to bleeding in women with PPH and in patients with traumatic bleeding, without an increase in adverse events. The WOMAN trial recruited 20,060 women with PPH and showed that TXA reduces the death due to bleeding (RR=0.81, 95% CI 0.65 to 1.00), especially when administered within three hours of giving birth (RR=0.69, 95% CI 0.52 to 0.91)
^
8
^. The CRASH-2 trial randomised 20,211 patients with trauma and showed that TXA reduces deaths due to bleeding when given soon after injury
^
25,
26
^. The combined evidence from 40,138 patients recruited in the WOMAN and CRASH-2 trials indicates that TXA significantly increases survival from bleeding (odds ratio [OR]=1·20, 95% CI 1·08–1·33; p=0·001), the effect increases to 70% when the treatment is immediate after injury/childbirth (OR=1·72, 95% CI 1·42–2·10; p<0·0001)
^
9
^. In surgery, intravenous TXA reduces blood loss (RR=0.66, 95% CI 0.65 to 0.67) and the need for transfusion (RR=0.62, 95% CI 0.58 to 0.68) by about a third
^
27,
28
^.

The most common potential side-effects reported by manufacturers to be associated with use of TXA according to frequency are diarrhoea, vomiting and nausea
^
29,
30
^.

Most of the TXA is excreted in the urine unchanged within 12 hours of administration. To prevent accumulation in cases of renal impairment, women with known renal insufficiency are excluded from participating in this study. In addition, because a single dose of 1 g (IV or IM) or 4 g (oral) is used in the WOMAN-PharmacoTXA trial, there will be no risk of accumulation.

The absolute risk of thromboembolism amongst pregnant and postpartum women is estimated to be around 2 to 3 per 1,000 woman-years. Even with a low risk, the incidence of thromboembolic events is four times higher amongst pregnant and post-partum women than in non-pregnant women of the same age
^
31
^. There was no increase in the risk of venous thrombosis in the participants treated with TXA in the WOMAN trial. Given that severe bleeding may lead to vascular occlusive events it is possible that, by reducing bleeding, TXA also reduces the risk of thrombosis
^
32
^.

TXA passes into breast milk in very low concentrations, approximately one hundredth of the concentration in maternal blood
^
33–
35
^. One study reported that growth and development parameters were similar in children exposed to TXA through breastmilk compared to unexposed children, with no long-term adverse events
^
33
^. No adverse events in breastfed babies were found in the WOMAN trial
^
8
^.

TXA administered to pregnant women crosses the placenta and TXA concentration in the umbilical cord blood is similar to the concentration in the maternal blood
^
36,
37
^. The half-life of TXA in serum is 1–2 hours
^
38
^, which would result in the elimination of TXA from the body within a few hours. Information is limited on the potential adverse effects on neonates of TXA administered to women before CS.

One study reported that no side effects were observed in new born babies from 12 healthy mothers who received TXA 10–20 min before CS delivery
^
36
^. In three trials, 1 g of TXA was administered 10–20 minutes before CS, and no adverse events to mothers and neonates were reported in two of them
^
34
^. One of the three studies reported that some mild and transient side effects occurred, but did not specify what kind of effects, how many participants were affected, and if any of these effects affected the babies
^
39
^. A systematic review on the prophylactic use of TXA in cases of elective CS or abdominal myomectomy included 16 trials with a total of 2,949 patients (2,789 underwent CS)
^
40
^. Only one of the eligible studies reported thromboembolic events that occurred in two patients in the TXA group, and two in the control group. This review did not report any side effects of prophylactic TXA on neonates. Similarly, a systematic review on the prophylactic use of TXA in women undergoing CS included 21 trials with a total of 3,852 patients
^
41
^. Also this review did not report any adverse events in the mothers, except for the four cases of thromboembolic events reported in the same trial included in the previous review. A review on guidelines and relevant data on the use of TXA in PPH prophylaxis for CS and vaginal delivery reported that the only evidence of possible adverse events for the mother concerned poor renal outcome in a case series study with 18 patients with renal cortical necrosis in PPH where a TXA maintenance dose was used. The case series study reported that patients that did not recover normal renal function had a TXA maintenance dose of 0.5–1 g/h for a longer time (7.1 ± 4.8 h) compared to patients who recovered partial renal function (2.9 ± 2.4 h)
^
42,
43
^. This review confirmed that there are no reports of adverse neonatal outcomes associated with the administration of TXA shortly before giving birth to prevent PPH
^
42
^. A systematic review on the effectiveness and safety of the use of TXA to prevent PPH that included 25 studies with a total of 4,747 participants concluded that there was no increased risk of deep vein thrombosis and an increased risk of minor transient events, i.e. nausea, vomiting, headache or dizziness
^
44
^. The included studies that evaluated the safety of TXA on neonates reported that no adverse events occurred, and the Apgar score that assesses the baby’s health immediately after birth showed no difference between babies in TXA-treated and control groups
^
44
^.

No mutagenic activity of TXA has been detected
*in vitro* and
*in vivo* test systems
^
45
^. No foetal abnormalities were identified in early dysmorphology and reproductive studies in animals
^
45–
47
^.

As the TXA will be delivered at the end of the 3rd trimester of pregnancy when the foetal development is complete, the trial treatment will not have any impact on foetal development.

The foreseeable risks related to the IM route of administration may include pain, redness and bruising at the injection site and a rare risk of infection at the injection site.

The study also involves additional blood samples from all participants. We will take the smallest possible volume of blood that will allow us to carry out the analysis. The total volume of blood taken from the participating women (maximum of 35 mL over 24 hours) should have no clinical impact on the participant. One blood sample (2 × 10 µl) will be taken from the neonate at the time of the routine heel prick test.

We will routinely assess all women for nausea, vomiting, diarrhoea, thrombotic events, seizures and injection site reactions as secondary outcomes. Additionally, all neonates will be routinely assessed for birth complications and adverse events.

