### Randomisation

After collecting baseline data, enrolled participants will be randomised into one of the four groups described in “Description of investigational product and justification of the dosage, route of administration, administration schedule and treatment duration”. The sequence for each dosing cohort will be created using computer-generated random numbers, using blocking to ensure the required balance in the allocation of participants to treatment arms. The allocation ratio will be 1:1:1:1. 

An IT coding expert supported by a statistician who are not involved in the conduct of the trial will prepare the randomisation codes. Eligibility will be confirmed and randomisation done via an online database. Once the code is generated, the trial intervention will be prepared and administered by a trained trial team member. Participants and all trial staff will be blind to treatment allocation until randomisation is completed.

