## Pharmacovigilance

Maternal events which occur as a consequence of the CS, or events which commonly occur in this population independent of exposure to the TXA administration, and those which are study endpoints do not need to be reported as an adverse event. Congenital or genetic abnormalities in neonates do not need to be reported as adverse events as these events are collected routinely. All other events fulfilling the criteria below should be reported. If a participant (both maternal and neonate) develops an adverse event, they should be treated in line with local procedures. In the definition below, participant refers to both maternal and neonate (s).

The flow chart of the safety reporting is shown in Additional file 6 (see
*Extended data*)
^
49
^.

More details on pharmacovigilance are available in Additional file 3 (see
*Extended data*)
^
49
^.

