### Safety parameters

**Full blood count and renal function parameters:** Descriptive statistics for baseline and follow-up will be presented for each laboratory parameter. Changes from baseline as well as shift tables for laboratory parameters will be presented. All laboratory values will be classified as normal, below normal (low), or above normal (high) based on normal ranges supplied by the central laboratory. Frequencies of abnormal values will be presented in tabular form. For purposes of analyses, laboratory results based upon standardized units will be used.

**Vital signs:** Descriptive statistics for blood pressure, heart, and respiratory rate will be presented in tabular form with mean, median, standard deviation and range (minimum and maximum) as appropriate. Number (%) of women with abnormal values in each randomised group will be presented.

**Expected adverse events (collected routinely as outcomes for all participant):** For each event, the number (%) of women in each randomised group will be presented.

**Other adverse events:** Adverse events will be coded by primary system organ class and preferred term using the Medical Dictionary for Regulatory Activities (MedDRA). The number of events (n) and number (%) of participants with events will be presented. Events will be presented separately for maternal and neonates.

**IM injection skin reaction:** Number (%) of women with a reaction and severity of reaction will be presented.

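### The routine maternal symptom list follows the manufacturer-reported effects but omits headache and dizziness, so these two may be incompletely recorded

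*Protocol article*

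**What the plan says.** In the protocol article, the Rationale section on the safety of TXA names three common side-effects reported by manufacturers: diarrhoea, vomiting and nausea. It then reviews trial evidence:

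- A systematic review of TXA to prevent PPH (25 studies, 4,747 participants) found "an increased risk of minor transient events, i.e. nausea, vomiting, headache or dizziness".
- Of a different review, covering 21 trials and 3,852 patients having a caesarean, the article says: "Also this review did not report any adverse events in the mothers, except for the four cases of thromboembolic events".

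The section ends with the commitment on collection: "We will routinely assess all women for nausea, vomiting, diarrhoea, thrombotic events, seizures and injection site reactions as secondary outcomes".

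Three other sections bear on how an unlisted symptom is handled:

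- Pharmacovigilance lists what need not be reported as an adverse event. It begins "Maternal events which occur as a consequence of the CS, or events which commonly occur in this population", and qualifies the second group as common independent of TXA exposure. It adds that "those which are study endpoints do not need to be reported as an adverse event". Other events meeting the reporting criteria are to be reported.
- Safety parameters has one heading for "Expected adverse events (collected routinely as outcomes for all participant") and another for other adverse events, which are MedDRA-coded: "The number of events (n) and number (%) of participants with events will be presented".
- Randomisation states: "Participants and all trial staff will be blind to treatment allocation until randomisation is completed". Trial design calls the study open label.

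**The concern.** The article cites a grouped finding of four symptoms and carries only two of them into routine assessment, without giving a reason. A listed symptom is collected as an outcome for every woman. An unlisted one has to be volunteered or noticed, and must then pass a judgement on whether it needs reporting at all. That judgement concerns cause and background frequency, and it is made by people who know which arm the woman is in.

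Safety of the three routes is a secondary objective, and the no-TXA arm of 30 women is the safety control. For headache and dizziness, a low count, or a difference between arms, could therefore partly reflect what staff chose to report. The primary pharmacokinetic endpoint and the sample size are not involved.

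**Working it through.** There is no planned figure to reproduce. The check is a comparison of lists, then a trace of how an unlisted symptom would be recorded.

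**1. The lists** (all from the safety section under Rationale)

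| Symptom | Manufacturers' common effects | Review of 25 studies | Routine list |
|---|---|---|---|
| Nausea | yes | yes | yes |
| Vomiting | yes | yes | yes |
| Diarrhoea | yes | no | yes |
| Headache | no | yes | **no** |
| Dizziness | no | yes | **no** |

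The other three routine items are thrombotic events, seizures and injection site reactions, so the list has 3 + 3 = 6 items. All 3 manufacturer-reported effects are on it. Of the review's 4 symptoms, 2 are on it and 4 − 2 = 2 are not.

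**2. Elsewhere in the article.** Neither headache nor dizziness is named again in the secondary endpoints, the follow-up assessments or the safety analyses.

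**3. The remaining route.** Maternal adverse events are a secondary endpoint, recorded for up to 7 days. On the article's text, an unlisted symptom enters there, subject to the Pharmacovigilance exclusion. The qualifier about TXA exposure can be read in two ways:

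- Events that are common whether or not TXA is given. A headache after a caesarean could then be left out in any arm, if headache is common in these women. That is an assumption, since the article gives no rate.
- Only events unrelated to TXA. Staff must then decide whether a given headache or dizzy spell is related.

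Either reading needs a judgement, and it is made after allocation is known. A listed symptom does not depend on it. Listed symptoms may also be excused from adverse event reporting as study endpoints, but they are still collected as outcomes.

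**4. What a change during recruitment would yield.** Recruitment runs from 18 December 2020 to a planned end on 30 June 2021: 13 + 31 + 28 + 31 + 30 + 31 + 30 = 194 days. Assume even accrual of 120 women, with women asked = 120 × (1 − fraction of the period elapsed):

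| Change in force after | Women asked | Per arm (÷ 4) |
|---|---|---|
| 25% | 90 | 22.5 |
| 50% | 60 | 15 |
| 75% | 30 | 7.5 |

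These figures describe the coverage of a late change. They say nothing about how many events would be missed without it.

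**The case against.** The strongest case against is that the list is a coherent choice: the manufacturers' common effects, the serious risks and the route-specific reactions. The review result is grouped, so it does not show that headache or dizziness rose on its own, and the cited review of 21 trials in women having a caesarean reported no maternal events other than thromboembolic ones. Adverse events are still recorded, coded, followed up and reviewed by an independent data monitoring committee. The exclusion says that events need not be reported; it does not bar reporting them. The case report form and the full pharmacovigilance text are not shown, and Safety parameters does not enumerate the expected events.

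Most of this stands and limits the point. It explains where the list came from, but not why half of a finding cited in the same section was left out. The general route is real, but it is unsolicited and subject to the exclusion.

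Three stronger readings are tempting, and the documents support none of them:

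- *That the two symptoms are not collected, or can only ever be classed as other adverse events.* The first ignores general reporting. The second cannot be established without the case report form.
- *That women without TXA are observed less, because they give only a baseline pharmacokinetic sample.* The article also lists 5 D-dimer, 2 full blood count and 2 renal samples (9 in all) and does not confine them to the TXA arms. The sampling figure is not shown, so contact by arm cannot be derived.
- *That routine questioning would remove bias between arms.* Women and staff know the allocation, so self-reported symptoms stay open to it. The main gain is completeness.

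**Conclusion.** The point holds in a limited form. The routine list omits two of the four symptoms that a review cited in the same section groups as increased with preventive TXA. On the article's text, their recording depends on unsolicited reports and on an unblinded judgement under the exclusion, so it may be incomplete. Neither the amount nor the direction of any distortion can be given.

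This rests on one assumption: that the case report form does not already ask about both symptoms. If it does, only the list in the safety section needs correcting. The matter is low priority, since these events are reported descriptively, as numbers and percentages.

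**What to change.** Unless the case report form already covers them:

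- Add headache and dizziness to the routinely assessed maternal outcomes in the safety section under Rationale.
- Ask about both in all four arms, whenever nausea, vomiting and diarrhoea are asked about.
- State in Pharmacovigilance that the exclusion for caesarean-related or common events does not apply to these two symptoms.
- Under the expected adverse events in Safety parameters, give the number of women asked in each randomised group, and the number (%) of those with each symptom.

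The cost is two yes/no items on the paper and electronic forms, within an assessment already made, and two rows in a planned table. If the change counts as a substantial amendment, regulatory and ethics approval must come first. Women enrolled before it takes effect will lack the items, so the denominators need to be shown. If it is too late to amend, the report should say that the two symptoms were not routinely assessed, so that a low count is not read as evidence of absence.
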